### Ethical Considerations

The trial is being conducted in accordance with ethical principles derived from the Declaration of Helsinki and is in line with Good Clinical Practice and applicable regulatory requirements. The clinical research ethics committee of Women’s Hospital, School of Medicine, Zhejiang University has reviewed the trial protocol, and full ethical approval has been granted (IRB-20230198-K). Each woman identified as eligible for the study is required to give written informed consent, including but not limited to, for primary data collection and secondary analyses of research data prior to inclusion in the trial.

Apart from sample collection and required assessments during follow-up, the study does not involve any further impact on the patients’ clinical procedures. The patients’ PE status will be kept confidential from laboratory technicians, and neither the investigator nor the patient will know the detection results, which ensures that the clinical therapeutic scheme and pregnancy outcomes will not be affected.

### Recruitment

Potential participants will be identified by the research team from the antenatal clinic at Women’s Hospital, School of Medicine, Zhejiang University. Eligible women must meet all inclusion criteria without violating any of the exclusion criteria (Textbox 1) and will be provided with the participant information and consent form to sign. A research team member will provide a verbal explanation of the trial, including a description of the trial processes, the voluntary nature of the trial, and that a decision of whether or not to participate will not affect normal clinical care. No trial-related procedures will be performed on any individual without their prior written informed consent. All participants will be followed up until 42 days postpartum.

Inclusion and exclusion criteria for determining trial eligibility.Inclusion criteriaAged ≥18 years.Gestational week 20+0 to 33+6.Signed written informed consent.Single pregnancy.Clinically suspected preeclampsia (PE), meeting one or more of the following criteria:(i) new onset of elevated blood pressure (systolic ≥130 mmHg and/or diastolic ≥80 mmHg);(ii) aggravation of preexisting hypertension (increase of more than 30 mmHg systolic/15 mmHg diastolic from the basic blood pressure in patients without hypertension, or a significant increasing trend or increase beyond the controlled level based on the original treatment for patients with hypertension);(iii) new onset of proteinuria (no urinary tract infection);(iv) one or more clinical symptoms indicate suspected PE (other possible causes have been ruled out): upper abdominal pain, headache with impaired vision, fetal growth restriction, thrombocytopenia (platelets count<100×10^9^/L), liver function impairment (elevated blood concentrations of liver transaminases up to twice the normal concentration), and renal impairment (serum creatinine>1.1 mg/dL or a doubling of the serum creatinine concentration in the absence of other renal disease).Exclusion criteriaConfirmed diagnosis of PE/chronic hypertension with PE (superimposed PE).Confirmed diagnosis of eclampsia.Confirmed diagnosis of hemolysis with a microangiopathic blood smear, elevated liver enzymes, and low platelets (HELLP syndrome).Fetal chromosomal abnormalities.Concomitant participation in another clinical study.Received investigational intervention drugs in the past 3 months.Visible hematuria.Preexisting renal disease.

### Sample Size

The target negative predictive value (NPV) is 99% and the target positive predictive value (PPV) is 54.0%. A positive test rate of 15% is assumed. The Type I error is set to .05. A sample size of 280 should be sufficient to detect NPV>90% and PPV>25% with 80% power. Therefore, at least 300 eligible participants will be included in this study considering a dropout rate of 6%. To avoid an overrepresentation of cases of late-onset PE, no more than 50% of the enrolled participants will be at 32 weeks gestation or above and no less than 20% of the enrolled participants will be at gestational week below 28+0 at inclusion.

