With increasing knowledge of the condition, six stages of PE have been proposed [6]. Defective placentation (stage 3) results in oxidative stress, and placental-derived products are released into the maternal blood (stage 4) before PE is diagnosed (stage 5). Recently, an increased level of misfolded proteins in the urine has been identified in patients with PE [18], suggesting that PE might share pathophysiologic features with recognized protein misfolding disorders such as Alzheimer disease. In patients with PE, misfolded proteins such as amyloid beta and transthyretin can accumulate in the circulation to exert neurotoxic effects and activate inflammatory cascades, leading to endothelial dysfunction and oxidative stress. Buhimschi et al [18] demonstrated that a dot test using Congo Red, a synthetic diazo dye with specific affinity for misfolded proteins, to visualize this aggregation feature (ie, congophilia) for detecting the presence of misfolded proteins in urine could serve as a promising diagnostic tool for PE. Li et al [19] subsequently developed a simple and rapid point-of-care testing (POCT) tool to detect the presence of misfolded proteins in urine based on visual observation, which achieved an overall sensitivity of 73.6% that reached up to 83% for severe PE cases.

The traditional approach for PE screening is to identify risk factors based on maternal demographic characteristics and medical history; however, this approach can only identify 35% of total PE cases and 40% of preterm PE cases, with a false-positive rate of approximately 10% [20,21]. A noninvasive laboratory method involving measurement of the ratio of soluble FMS-like tyrosine kinase 1 (sFLT-1) to placental growth factor (PlGF) in the urine proved to be effective in PE diagnosis, achieving a sensitivity of 70%-72.5% with a 5%-14% false-positive rate [22,23]. Thus, combining urine PlGF and sFLT-1 testing with other biomarkers may yield the best predictive performance.

In this trial, we will test a new congophilia-based detection method alone or combined with clinical variables and other urine biomarkers to predict the onset of PE before its clinical manifestation. This work can therefore help clinicians better identify PE earlier, enabling the proactive management and monitoring of pregnant women who exhibit signs or symptoms of PE but do not meet the current diagnostic criteria.

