### Statistical Analysis

All variables will be compared between case and control groups. Either parametric or nonparametric tests will be applied for continuous variables and *χ*^2^ tests will be used for categorical variables. Receiver operating characteristic analysis will be used when applicable. Univariable or multivariable logistic regression will be applied to develop the prediction models. All *P* values will be two-tailed. The statistical analysis will be run on SPSS version 27 (IBM) statistical software.

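### At the PE incidence implied by the sample size inputs (8.95%), the NPV>90% bar lies below the NPV of an uninformative test (91.05%), and the stated 80% power at n=280 recomputes to about 96%

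*Protocol article*

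**What the plan says.** All figures are in the Protocol article, Sample Size section. The targets are given as "The target negative predictive value (NPV) is 99" and "the target positive predictive value (PPV) is 54.0" (both per cent). On the share of positive results it says "A positive test rate of 15% is assumed", and on the error rate "The Type I error is set to .05". It then concludes: "A sample size of 280 should be sufficient to detect NPV>90% and PPV>25% with 80% power". Enrolment is raised to at least 300 to allow for 6% dropout.

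The section names no PE incidence, no test and no sidedness. The Statistical Analysis section says that P "values will be two-tailed", which may or may not also describe the sample size calculation. The Objective section makes short-term rule-in and rule-out the primary aim. The classification of cases and controls counts PE from the first visit to 42 days postpartum.

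**The concern.** An NPV has meaning only against the proportion of women who stay free of PE anyway. A test that ignores PE has an NPV of 1 minus the incidence. A rule-out bar below that value can be met without the test contributing anything. The bar here is a round 90%, not set against any incidence, yet the other inputs fix the incidence, so the comparison can be made.

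At stake is how the rule-out half of the primary objective would be reported. If NPV>90% is presented as a result in its own right, it would be read as support for rule-out when it need not be.

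The second matter is that the quoted power looks too low for the distance between the targets and the bounds (54% against 25%, and 99% against 90%). The sample size statement could then not be traced to its inputs.

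**Working it through.** **Inputs** (Sample Size section): target NPV 0.99, target PPV 0.54, positive rate 0.15, bounds NPV 0.90 and PPV 0.25, Type I error 0.05, n = 280, power 0.80. Expected positives: 280 × 0.15 = 42. Expected negatives: 280 − 42 = 238.

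**1. Dropout.** 280 / 0.94 = 297.9, so 298; enrolling at least 300 is consistent.

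**2. The stated power.** Each leg is taken as a one-sample exact binomial test against its fixed bound, at two-sided 0.05 (0.025 in the relevant tail).

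- PPV: 42 positives, null 0.25. Reject at 17 or more PE cases. Power at 0.54 is 97.2%.
- NPV: 238 negatives, null 0.90. Reject at 224 or more PE-free women (224/238 = 94.1%). Power at 0.99 exceeds 99.99%.
- The joint power is therefore governed by the PPV leg.

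| Error rate | Joint power, 42/238 fixed | Joint power, positives ~ Binomial(280, 0.15) |
|---|---|---|
| one-sided 0.05 | 98.7% | 98.0% |
| two-sided 0.05 | 97.2% | 96.0% |
| two-sided 0.05, Bonferroni | 94.5% | 93.6% |

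Normal, Wald, continuity-corrected and arcsine versions over the same error rates give 93.7% to 99.0%. None is near 80%. With random positives, 80% joint power needs about 164 women at two-sided 0.05, or 136 at one-sided 0.05.

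One formula does land near 80%: a two-sample, two-sided comparison of 54% with 25% at 42 per group gives 78.6% (pooled variance) or 81.2% (unpooled). That may be where 280 came from, but this is conjecture. The section describes fixed bounds and no comparator group, so the formula would not fit.

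**3. The implied incidence.** Incidence = positive rate × PPV + negative rate × (1 − NPV) = 0.15 × 0.54 + 0.85 × 0.01 = 0.0810 + 0.0085 = 0.0895.

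**4. The no-information NPV.** 1 − 0.0895 = 0.9105, above the 0.90 bar. At this incidence and positive rate, an NPV of exactly 0.90 goes with a PPV of (0.0895 − 0.85 × 0.10) / 0.15 = 0.030, which is below the incidence and so worse than chance.

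**5. What each leg screens out** (42/238, two-sided 0.05). An uninformative test has NPV 0.9105 and PPV 0.0895.

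- It passes the NPV leg with probability 5.5%, against 1.7% when the true NPV is 0.90.
- It passes the PPV leg with probability about 4 × 10⁻⁸.

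A true PPV of 25% at the same margins forces an NPV of 1 − (0.0895 − 0.15 × 0.25) / 0.85 = 93.9%. A test that truly meets the PPV bound is therefore informative already, and the 90% bar adds nothing to that.

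**6. Dependence on incidence.** The bar equals the no-information NPV at an incidence of 10%. If PPV and NPV sat at the two bounds, the incidence would be 0.15 × 0.25 + 0.85 × 0.10 = 12.25% and the no-information NPV 87.75%, below the bar.

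**7. Effect of a tied bar.** With the bar at 0.9105 and 238 negatives, the NPV leg is passed from 226 upward (95.0%). Its power at 0.99 stays above 99.9%, so joint power with random positives remains about 96%.

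**The case against.** The strongest reply is that the section sets the two bounds together. A reader might infer that a useless test could meet the plan's criterion. The documents do not support that, because such a test practically never passes the PPV leg. Even on the NPV leg alone, the plan's own figures give a pass rate of 5.5%. Much higher rates need lower incidences over a short horizon (79% at an assumed 5%), and no such incidence is given; the case definition runs to 42 days postpartum. The 91.05% is also tied to the target values and reverses above 10% incidence. All of this stands, and it confines the point to the NPV bar taken alone at the assumed incidence.

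It is equally true that the power misstatement harms nobody: 280 is more than 80% power requires. A reader who infers an underpowered study would be wrong. Nor does the power figure bear on rule-out value; the two matters are separate.

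Two further inferences fail:

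- The inputs imply a sensitivity of 0.081/0.0895 = 90.5%, whereas the Background cites a visually read tool "which achieved an overall sensitivity of 73.6% that reached up to 83% for severe PE cases". That figure comes from a different setting from prediction in suspected PE, so it does not contradict the targets.
- The Statistical Analysis section says "All variables will be compared between case and control groups" and mentions no test of NPV or PPV against the bounds. That detail may sit in an analysis plan that is not shown, so its absence from an article is not an error.

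What the reply leaves untouched is that the 90% figure is the only numerical rule-out bar in the article, and that it lies below the no-information value at the incidence its own inputs imply.

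**Conclusion.** The point holds in limited form. At the implied incidence of 8.95%, the NPV>90% bar is 1.05 percentage points below the NPV of an uninformative test (91.05 − 90). Taken alone it gives no evidence of rule-out value, and within the joint criterion only the PPV leg screens out an uninformative test. This rests on the stated targets and 15% positive rate; above 10% incidence the bar would carry information.

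The 80% power is also wrong as written. Exact joint power is about 96% at two-sided 0.05, or 94% to 98% across the error-rate choices when the number of positives is random. The error is in the safe direction and the sample size is adequate. The passage should be corrected, but neither matter undermines the design.

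**What to change.** Keep n at 280 evaluable and at least 300 enrolled. In the Sample Size section:

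1. State the implied PE incidence (about 9%) and the horizon to which it applies.
2. Restate the power as about 96% jointly, naming the test and its sidedness.
3. Replace the fixed 90% by a bar tied to incidence: test that NPV exceeds 1 minus the cohort's PE incidence for the chosen horizon. Equivalently, test that PE risk in test-negative women is below the whole-cohort risk. If incidence is estimated from the same women, the analysis must treat it as estimated; the 96% is for a fixed bound of 91.05%.
4. Say explicitly that both the NPV and the PPV leg must succeed.

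The cost is wording and a slightly stricter NPV standard. According to the Results section, analysis starts only after follow-up is complete, so at the time of the article the bar could be reset without sight of results.

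The tied bar is a floor: it shows that the test informs, not that the residual risk is low enough for use. A higher fixed bar is optional. NPV>95%, for example, keeps joint power of about 92% at the sponsor's targets, but NPV power falls to about 18% to 34% if the true NPV is 96.6% to 97.2% (an assumed range). That is a judgement for the sponsor.

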### Study Groups: Classification of Cases and Controls

Standard diagnostic criteria [24,25] for PE are new onset of hypertension (systolic blood pressure≥140 mmHg or diastolic blood pressure≥90 mmHg measured on two occasions at least 4 hours apart) and new-onset proteinuria (≥300 mg/day or protein/creatinine ratio ≥0.3 mg/dL) after 20 weeks of gestation. Diagnostic criteria in the absence of proteinuria include any of the following: (1) thrombocytopenia (platelets count<100×10^9^/L); (2) liver function impairment (elevated blood concentrations of liver transaminases to twice the normal concentration); (3) renal insufficiency (serum creatinine>1.1 mg/dL or a doubling of the serum creatinine concentration in the absence of other renal disease); (4) pulmonary edema; and (5) central nervous system abnormalities or visual disturbances.

Cases are defined as patients who develop PE at any time between the first visit to 6 weeks (42 days) postpartum.

Controls are patients who do not develop PE throughout the pregnancy and up to 6 weeks (42 days) postpartum.

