**Objective:**

The main purpose of this trial is to evaluate the value of the urine congophilia-based detection of misfolded proteins for the imminent prediction of PE in women presenting with suspected PE. The secondary objectives are to demonstrate that the presence of urine misfolded proteins correlates with PE-related maternal or neonatal adverse outcomes, and to establish an accurate PE prediction model by combining misfolded proteins with multiple indicators.

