### Objective

The primary objective of this study is to assess the short-term predictive potential of the new congophilia-based detection tool for PE onset in pregnant women with a clinical suspicion of PE. That is, we aim to confirm whether the urine misfolded protein level can be used to rule in or rule out PE in the short term. The secondary objectives are to evaluate whether the urine misfolded protein level correlates with PE-related maternal or neonatal adverse outcomes and to establish an accurate PE prediction model by combining misfolded protein values and multiple indicators.

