### Outcome Measures

The primary outcome is the onset of PE after study inclusion. The secondary outcomes are the following maternal and fetal adverse outcomes: maternal death, pulmonary edema, acute renal failure, cerebral hemorrhage, cerebral thrombus, disseminated intravascular coagulation, eclampsia, HELLP syndrome, rupture of placenta, placental abruption, perinatal death, stillbirth, intrauterine growth restriction, small for gestational age, respiratory distress, necrotizing enteritis, intraventricular hemorrhage or subdural and cerebral hemorrhage, neonatal hypoxic encephalopathy, or periventricular leukomalacia. In addition, the date and mode of delivery, fetal weight, and Apgar score are important outcome measures.

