### Data Collection

Participant data for this study will be collected by investigators and input into an electronic case report form (eCRF). The data will be verified by the principal investigator when suspicious data entries are noted. The data manager will check the completion of the data for final analysis. The study will include 6 visits plus a postpartum documentation. The first visit starts at enrollment, followed by 4 visits once a week when participants come for their routine prenatal examinations. There will be one visit at delivery as well as one postpartum documentation. On occurrence of pregnancy complications, further visits are possible. The clinical data to be collected during each visit are summarized in Table 1. The time interval between two consecutive visits could be 7±2 days, and adherence to the time schedule is crucial for incorporating participant data into the final analysis.

**Table 1 table1:** Summary of the data collection procedure and timeline.

Data collected	Visit 1	Visit 2	Visit 3	Visit 4	Visit 5	Delivery	Postpartum	Unscheduled visit
Inclusion/exclusion criteria	✓							
Informed consent	✓							
General baseline feature	✓							
Chronic history	✓							
Pregnancy history	✓							
Concomitant medication	✓	✓	✓	✓	✓	✓	✓	✓
BMI	✓	✓	✓	✓	✓			✓
Blood pressure	✓	✓	✓	✓	✓		✓	✓
Sampling and detection	✓	✓	✓	✓	✓			✓
Preeclampsia assessment	✓	✓	✓	✓	✓	✓	✓	✓
Laboratory parameters (blood and urine)	✓	✓	✓	✓	✓			✓
Sonographic data	✓	✓	✓	✓	✓			✓
Delivery outcome						✓		
Pregnant woman status						✓	✓	
Fetal/neonatal status						✓	✓	

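### The primary objective is short-term rule-in and rule-out of PE, but case status has no short-term window and runs to 42 days postpartum

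*Protocol article*

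**What the plan says.** The Objective section of the Introduction says the study will "assess the short-term predictive potential of the new congophilia-based detection tool for PE onset in pregnant women with a clinical suspicion of PE", and restates this as whether the test "can be used to rule in or rule out PE in the short term". The abstract gives the aim as "imminent prediction of PE in women presenting with suspected PE", and the closing Conclusions again describe a short-term tool. None of these places gives the short term a length.

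Outcome Measures states: "The primary outcome is the onset of PE after study inclusion". Study Groups states: "Cases are defined as patients who develop PE at any time between the first visit to 6 weeks (42 days) postpartum". Controls must stay free of PE over that same span. Statistical Analysis then compares variables between these two groups.

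Entry is at 20+0 to 33+6 weeks (Recruitment, Textbox 1). Urine is taken at enrolment and at four weekly visits, with 7±2 days between visits (Data Collection). Sample Size plans on 15% positive tests, PPV 54% against a bound of 25%, and NPV 99% against a bound of 90%. No time horizon is attached to any of these figures.

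**The concern.** A predictive value has no meaning without a horizon. NPV for the next few weeks and NPV for the rest of pregnancy plus the puerperium are different quantities, and the clinical claim in the objective is about the first. The stated case rule delivers the second.

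The effect on a given set of urine results has a known direction. Lengthening the window can turn non-cases into cases but never the reverse. The whole-pregnancy definition can therefore only lower NPV or leave it unchanged, and only raise PPV or leave it unchanged, compared with a short window. A woman who tests negative at 22 weeks and develops PE at 38 weeks is scored as a rule-out failure, even if the test was right for the following month. A woman who tests positive at 22 weeks with the same course is scored as a correct rule-in, although nothing was imminent.

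The horizon also differs between women according to gestational age at entry, so the pooled NPV and PPV are averages over unequal lengths of follow-up.

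**Working it through.** **1. Length of the outcome horizon.** Entry limits: 20+0 weeks = 140 days and 33+6 weeks = 237 days. The article gives no delivery date; assume 40 weeks = 280 days.
- Entry at 20+0: 280 − 140 = 140 days to delivery; with 42 days postpartum, 182 days.
- Entry at 33+6: 280 − 237 = 43 days to delivery; with 42 days postpartum, 85 days.
- Sampled period: 4 × 7 = 28 days nominal (4 × 5 = 20 to 4 × 9 = 36 days with the visit tolerance).

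The outcome horizon is thus about 3 times (85/28) to 6.5 times (182/28) the sampled period. Time at risk before delivery differs about threefold between women (140/43 = 3.3).

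**2. The plan's own sample size.** At two-sided 0.05 and 80% power, PPV 54% against 25% needs 20 to 26 positives (score to exact binomial), or about 134 to 174 women at 15% positive. NPV 99% against 90% needs 54 to 56 negatives, about 64 to 66 women. So 280 does not reproduce as a minimum, but it is sufficient on the stated inputs (exact joint power about 96%). Dropout agrees: 280/0.94 = 298, hence at least 300. This does not bear on the present point.

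**3. PE rate implied by the planning inputs.**
- PE = positive rate × PPV + negative rate × (1 − NPV) = 0.15 × 0.54 + 0.85 × 0.01 = 0.0810 + 0.0085 = 8.95%, or about 25 of 280 women.
- Implied sensitivity = 0.0810/0.0895 = 90.5%.
- Implied specificity = 0.85 × 0.99/(1 − 0.0895) = 0.8415/0.9105 = 92.4%.

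The article does not say whether 8.95% is meant for a few weeks or to 42 days postpartum.

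**4. Conditional illustration over a longer window.** The article gives no PE rate for this population, so the rates below are assumptions.

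(a) Keep 15% positive. The best possible test makes every positive a case, so the remaining cases fall among the 85% negatives:
- NPV 99% requires PE ≤ 0.15 + 0.85 × 0.01 = 15.85%.
- NPV 90% requires PE ≤ 0.15 + 0.85 × 0.10 = 23.5%.

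(b) Keep the implied sensitivity and specificity instead and let the positive rate move. At 20% PE:
- NPV = 0.9242 × 0.80/(0.9242 × 0.80 + 0.0950 × 0.20) = 0.7394/0.7584 = 97.5%, with about 24% positive.
- At 30% PE, NPV is 95.8%, with about 33% positive.

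Under (b) NPV drops below the 99% target but stays above the 90% bound.

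**5. What a shorter window demands.** At 15% positive, PPV 54% needs at least 0.15 × 0.54 = 8.1% PE inside the window, and PPV above 25% needs more than 0.15 × 0.25 = 3.75%.

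**The case against.** The strongest reply is that nothing is lost. Urine and PE assessment are repeated weekly for about four weeks, so a windowed analysis needs no new data. The article also does not label NPV and PPV as primary, and a fuller protocol or analysis plan could add a window. The first part stands: this is a definition to be stated, not missing information. The rest does not remove the point. NPV and PPV are the measures that match a rule-in/rule-out objective and the only ones with targets, and the article fixes primary outcome and case status explicitly, over a span that its objective does not describe.

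A reader might also infer several stronger claims that the article does not support:
- **The targets are unreachable.** That follows only if 15% positive is kept and PE exceeds 15.85% or 23.5%, and no PE rate is given. Holding PPV at 54% as well gives NPV 86.0% at 20% PE (1 − (0.20 − 0.081)/0.85), but it places every additional case among the test-negatives. Calculation 4(b) points the other way, though it assumes that an early urine detects remote PE as well as imminent PE.
- **PE present on the day of the first visit counts as a case.** The wording of the case rule is loose, but confirmed PE is an exclusion criterion and the primary outcome is onset after inclusion.
- **Late PE is not ascertained.** Table 1 schedules a PE assessment at delivery and postpartum and allows unscheduled visits.
- **The enrolment quota fails.** The limit that "no more than 50% of the enrolled participants will be at 32 weeks gestation or above" aims to avoid overrepresentation of late-onset PE, not to exclude it. It governs age at entry, so it does not supply an outcome window either.

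**Conclusion.** The mismatch is in the current text and concerns the primary question. The objective is short-term, while case status covers everything from the first visit to 42 days postpartum. If delivery is near 40 weeks, that is 85 to 182 days against a sampled period of about 28. Relative to a short window, the rule can only push NPV down and PPV up, or leave them unchanged. The size of the shift cannot be computed, because the article gives neither a window nor a PE rate for any horizon; the thresholds of 15.85% and 23.5% are conditional on 15% positive tests. The point should be settled before analysis, since a window chosen after results are known would be data-driven.

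**What to change.** Before analysis:
1. Define primary case status as PE onset within a fixed number of days after a named index urine, matched to the sampled period (for example about 4 weeks after the visit 1 sample). State how women who deliver without PE inside the window are classified.
2. Keep PE at any time to 42 days postpartum as a secondary outcome.
3. State which horizon the 15%, 54% and 99% planning figures refer to, and recheck them for the chosen window. The targets should not simply be carried over: at 15% positive, PPV 54% needs at least 8.1% PE within the window.

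The change is mainly one of wording, because PE assessment is already scheduled at each sampling visit and the article says analysis starts only after follow-up is complete. The cost is statistical: a shorter window gives fewer primary events, hence a lower attainable PPV and a wider PPV interval.
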